#### Interim analyses {21b}

There are no interim analyses planned.

#### Methods for additional analyses (e.g., subgroup analyses) {20b}

There are no subgroup analyses planned.

#### Methods in analysis to handle protocol non-adherence and any statistical methods to handle missing data {20c}

Missing data will not be imputed. All available data will be used in the models.

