### Trial design {8}

We designed a two-arm RCT to evaluate the efficacy of the *MyKid’sNutrition* app. Following a baseline evaluation, children and their mothers will be randomly allocated to either the experimental group, *MyKid’sNutrition* app in addition to treatment as usual (TAU), or TAU alone as the control group. The patient allocation ratio will be 1:1. Figure 1 represents the *MyKid’sNutrition* RCT flowchart.

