#### Criteria for discontinuing or modifying allocated interventions {11b}

All subjects will be free to leave the study at any phase of the study for any reason without any consequences. Also, the research team will be free to remove any subject if they are uncooperative or lost to follow-up.

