#### Sample size {14}

To estimate the sample size, we performed a statistical power analysis based on previous studies [24] and considering an alpha equal to 0.05 and a power of 0.80 with an effect size of 0.5 using G*Power 3.1.9.7. Accordingly, the sample size was estimated as 102 participants (51 mother–child pairs in each group). Finally, considering a dropout rate of 14%, the total sample size was calculated as 116 people.

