### Statistical methods

#### Statistical methods for primary and secondary outcomes {20a}

We will use descriptive statistics for summarizing and determining the sample’s characteristics and distribution among the patients. Frequencies and proportions will be used to summarize categorical data. Analyzing associations between qualitative data variables will be done using the chi-square (*χ*^2^) test or Fisher’s exact test, as appropriate. The unpaired *t*-test or Mann–Whitney *U* test will be used to analyze quantitative data between the two independent groups. The analyses will be adjusted for age, sex, and other baseline characteristics as covariates when needed. A 95% confidence interval will be provided for all comparative analyses, and statistical significance for main effects will be determined as 5%.

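### With one follow-up visit and baseline adjustment left optional, the planned comparison of children seen at 3 months is open to bias if dropout differs by arm; a mandatory baseline covariate closes most of this gap

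*Protocol article*

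**What the plan says.** Protocol article, section 20c, gives the whole missing-data rule: "Missing data will not be imputed. All available data will be used in the models". Section 12 (Outcomes) has the growth z-scores and the mothers' scores measured at baseline and once more, at 3 months. It frames the outcomes as change within groups and the difference between groups.

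Section 20a says that an unpaired t-test or Mann–Whitney U test "will be used to analyze quantitative data between the two independent groups". It then permits adjustment for age, sex and further baseline characteristics, but only where this proves necessary. It does not name the baseline value of the outcome among them.

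Section 14 (Sample size) deals with dropout by enlarging the sample: "Finally, considering a dropout rate of 14%, the total sample size was calculated as 116 people". Section 11b adds that "the research team will be free to remove any subject if they are uncooperative or lost to follow-up". Sections 17a and 17b describe an open-label trial in which only outcome assessors and analysts are blinded.

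**The concern.** With a single post-baseline visit, no imputation and a two-group test, the children compared are those who came back at 3 months. The protocol does not say this in so many words, but it follows from sections 12, 20a and 20c together. Enlarging the sample protects power. It does nothing about who is missing.

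Mothers and the research team know the allocation, and that team may remove uncooperative participants. Reasons for leaving, or rates of leaving, could therefore differ between the arms. If they also relate to the child's nutritional status, the returning children in the two arms are no longer comparable, and part of any observed difference (or of a null result) would reflect who returned.

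The analysis that guards against the simplest form of this, adjustment for the baseline value of the outcome, is allowed by section 20a but not fixed.

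**Working it through.** **The plan's own figures.** Inputs from section 14: "considering an alpha equal to 0.05 and a power of 0.80 with an effect size of 0.5"; from section 8, 1:1 allocation. A two-sample t-test with these inputs needs 51 per arm, 102 in total, if one-sided, which matches the stated 102. The two-sided figure is 64 per arm, 128 in total; that is a separate matter and not pursued here. The stated 116 is 102 × 1.14 = 116.28, rounded down. After 14% loss, 116 × 0.86 = 99.8 children remain, about 50 per arm.

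**Assumptions for the bias check.** The documents give neither a dropout mechanism nor a correlation. Assumed: outcome SD 1; baseline-to-3-month correlation ρ = 0.7; 14% dropout per arm unless stated; logistic dropout with log-odds slope 0.5 or 1.0 per SD.

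**Formula when dropout depends on baseline.** Let m be the mean baseline value of returning children minus that of all children randomised to the arm, and D = m(app) − m(control). Then:
- bias in the 3-month difference = ρ × D
- bias in the change difference = (ρ − 1) × D
- bias in a linear model with baseline as covariate = 0

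If the arms lose children in the same way, D = 0 and nothing is biased.

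**Numbers for opposite directions by arm.**
- Slope 0.5: m = ±0.068, so D = 0.136. 3-month value: 0.7 × 0.136 = 0.095. Change: −0.3 × 0.136 = −0.041.
- Slope 1.0: m = ±0.124, so D = 0.249. 3-month value: 0.7 × 0.249 = 0.174. Change: −0.3 × 0.249 = −0.075.

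Simulations agree to rounding (0.095 and 0.175 on the 3-month value; −0.039 and −0.075 on change; 0.001 and 0.000 baseline-adjusted). Against the planned 0.5, the 3-month bias is 0.095/0.5 = 19% to 0.175/0.5 = 35%.

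**Other mechanisms.** Simulated with 2,000,000 children per arm, slope 1.0 and no imputation. Bias is app minus control, in SD; in the control arm the lower-scoring children leave more often.

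| Dropout depends on | 3-month value | Change | Baseline-adjusted |
|---|---|---|---|
| Baseline, alike in both arms | 0.00 | 0.00 | 0.00 |
| 3-month value, same slope and rate | 0.00 | 0.00 | 0.00 |
| Baseline, control arm only | −0.09 | +0.04 | 0.00 |
| Baseline, opposite directions | −0.17 | +0.08 | 0.00 |
| Baseline, same slope, 21% control vs 7% app | −0.08 | +0.03 | 0.00 |
| 3-month value, control arm only | −0.12 | −0.04 | −0.06 |
| 3-month value, opposite directions | −0.25 | −0.07 | −0.13 |
| 3-month value, same slope, 21% vs 7% | −0.12 | −0.04 | −0.06 |

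One further case: a single dropout rule on the 3-month value in both arms gives no bias if the app does nothing. With a true effect of 0.5 (dropout 17% control, 11% app), the 3-month comparison is biased by −0.04.

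**Precision.** At ρ = 0.7 the variance of the baseline-adjusted comparison is 1 − 0.7² = 0.51 of that for raw 3-month values. The corresponding factor for change is 2 × (1 − 0.7) = 0.60.

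**The case against.** Three stronger readings are tempting, and the documents do not support them.

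- *Any dropout related to nutritional status biases the test.* A reader might infer this, but it is not so. The first two rows of the table show zero bias when the dependence and the rate are the same in both arms.
- *The refusal to impute is the error.* With one follow-up value, an available-case model that adjusts for baseline is unbiased in every baseline-dependent scenario checked. Imputing from the same baseline variables would rest on essentially the same assumption, so it is not the needed remedy.
- *A missing sensitivity analysis is a fault.* Such detail commonly sits in an analysis plan or full protocol, neither of which is shown, so its absence from the article is no finding.

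The defence also has fair points on likelihood and size. No passage says that mothers will leave for different reasons by arm. The protocol plans regular contact, telephone and text follow-up, visit scheduling, an end-of-study report for everyone, and a consent question on using data after withdrawal. Section 12 speaks of change, for which the bias in the opposite-direction scenario is the smaller 0.04 to 0.08 SD. With about 50 per arm, the standard error of a raw difference is √(2/50) = 0.20 SD, larger than any of the opposite-direction figures for baseline-dependent dropout.

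Section 20a does allow covariates, so an unadjusted test is not the only analysis foreseen. What remains is that the allowance is conditional and does not name the one covariate that matters. Whether the protective analysis is run can therefore be settled after the data are seen.

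**Conclusion.** The concern holds in limited form. Sections 12, 20a and 20c together compare only children with a 3-month value, by a test that need not be adjusted for baseline. That comparison is biased if dropout depends on nutritional status differently by arm, if such dependence is combined with different dropout rates, or if dropout follows the outcome and the app changes it.

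The sizes, about 0.10 to 0.18 SD on the 3-month value and 0.04 to 0.08 SD on change, rest on the assumed correlation of 0.7, 14% loss per arm and opposite slopes of 0.5 to 1.0. They illustrate the problem and are not forecasts. The figures concern means; the Mann–Whitney test compares the same selected groups but was not simulated.

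The zero bias of the adjusted model assumes a linear relation to baseline that is common to both arms. Adjustment does not remove bias from dropout that depends on the unseen 3-month value differently by arm: about 0.06 to 0.13 SD remains.

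**What to change.** In section 20a, replace the t-test/Mann–Whitney comparison and the conditional adjustment with: *The main between-group analysis of each quantitative outcome is a linear model (ANCOVA) of the 3-month value on assigned arm, with the baseline value of the same outcome as a mandatory covariate. Every randomised pair with a 3-month value is included in the arm assigned, whatever their cooperation with the study.* Make section 11b consistent, so that removing a participant for being uncooperative does not remove an outcome that was measured.

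Optionally, let section 20c permit a sensitivity analysis that shifts missing 3-month values in either arm. This addresses the part that baseline adjustment cannot reach. As a guide to scale, if missing children in one arm would have been 0.5 SD worse than those seen, the shift is 0.14 × 0.5 = 0.07 SD.

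The main change costs only wording. The baseline values are already collected, no extra visits or participants are needed, and precision improves. The optional analysis adds a little work.

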#### Eligibility criteria {10}

The inclusion criteria will be as follows: children aged 2–6 years at baseline; mothers’ willingness to participate in the study and signing a written consent form; having a smartphone and willingness to use a smartphone application; mothers’ reading and writing skills; and confirmed malnutrition and underweight using growth charts.

There will be two exclusion criteria as follows: subjects suffering from a specific disease that can affect the results and those reluctant to continue participation in the study.

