#### Outcomes {12}

The outcomes of *MyKid’sNutrition* trial would be the change in the growth indicators and mothers’ nutritional knowledge, attitude and practice within the groups, and the differences between the groups. Weight for height and BMI for age *z*-scores, which are the growth indicators and mothers’ nutritional literacy, will be measured at baseline and after 3-month follow-up visits. Additionally, the participants’ demographic and socio-economic status will be measured.

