### Assignment of interventions: allocation

#### Sequence generation {16a}

Following baseline assessment, all eligible participants will be randomized (1:1 ratio) to intervention or usual care groups. The process of random sequence generation and the allocation of participants to intervention conditions will be implemented on an online platform by an independent researcher not involved in the process of subject recruitment.

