### Data collection and management

#### Plans for assessment and collection of outcomes {18a}

We will use a questionnaire to collect all participants’ sociodemographic and baseline information, including name, sex, age, contact information, family size and income, past medical history, phone number(s), education, and occupation. The research team will measure all children’s anthropometric indices and the presence of undernutrition will be assessed based on growth charts [6]. Using a questionnaire with confirmed psychometric properties, the mothers’ nutritional knowledge, attitude, and practice will be assessed [25]. All data will be collected in a uniform and reproducible manner by trained data collectors. The quality of the data will be supervised by the principal investigator.

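### The ban on imputation in {20c} has no exemption for baseline covariates, so an adjusted model would omit measured pairs that have a blank covariate

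*Protocol article*

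**What the plan says.** The protocol article, section {20c}, gives the whole missing-data rule in two sentences: "Missing data will not be imputed. All available data will be used in the models". It draws no line between outcomes missing at 3 months and values missing at baseline.

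Section {20a} sets the basic between-group analysis: "The unpaired *t*-test or Mann–Whitney *U* test will be used to analyze quantitative data". It then adds: "The analyses will be adjusted for age, sex, and other baseline characteristics as covariates when needed". Age and sex are named; the other covariates are left open.

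Section {18a} shows where those other characteristics would come from. The baseline questionnaire covers, besides sex and age, "family size and income, past medical history, phone number(s), education, and occupation".

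Two more statements bear on the point. Section {16a} puts baseline collection before allocation: "Following baseline assessment, all eligible participants will be randomized (1:1 ratio) to intervention or usual care groups". Section {12} says that the growth indicators and the mothers' nutritional literacy "will be measured at baseline and after 3-month follow-up visits".

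**The concern.** A regression can use a pair only if every variable in the model has a value. If an adjusted model includes family income or education, and income or education is blank for one mother, there are two ways to keep her pair: fill the value in or give it a category of its own. Read literally, {20c} forbids the first and does not provide for the second. The pair then leaves the model although its 3-month outcome is on file. The first sentence of {20c} thus defeats the second in exactly this setting.

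Precision is lost for no gain. The adjusted and unadjusted results would also rest on different sets of pairs, which makes it harder to tell the effect of adjustment from the effect of losing pairs. And the sample size in {14} allows for dropout only, so losses from blank covariates come on top of it.

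**Working it through.** **Which analyses are exposed**

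- The unpaired t-test and the Mann–Whitney test use no covariate. No pair is lost.
- Adjustment for age: age is an eligibility criterion ("children aged 2–6 years at baseline"), so it is known for every randomised child.
- Adjustment for sex: a basic baseline item, unlikely to be blank.
- Adjustment for any other questionnaire item: exposed wherever that item is blank.

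**Is filling legitimate here?** Baseline data are collected before randomisation, so whether a baseline value is blank cannot be a result of the arm. A fill that uses neither arm nor outcome therefore leaves the randomised comparison intact.

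**Inputs from {14}:** 102 evaluable pairs (51 per group), standardised effect 0.5, alpha 0.05. The plan states no figure for missing covariates, so there is none to reproduce. The 102 itself reproduces as a one-sided t-test (51 per group for 80% power); two-sided it would be 64 per group. That is a separate matter. Here 102 serves only as the number of measured pairs.

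**Assumed inputs, not in the documents:**

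- Within-arm outcome SD of 1.
- Baseline outcome with coefficient 0.6 and a second covariate with coefficient 0.2, both standardised and independent.
- Blanks on the second covariate, at random, in 10% or 20% of pairs.

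**Approximate standard error.** The residual variance is 1 − 0.6² − 0.2² = 0.60. For two equal arms with N pairs in total, SE ≈ √(4 × 0.60 / N).

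- N = 102, nothing missing: √(2.40/102) = 0.153.
- 10% deleted, N = 91.8: √(2.40/91.8) = 0.162.
- 20% deleted, N = 81.6: √(2.40/81.6) = 0.171.
- Second covariate left out altogether, all 102 kept (residual variance 0.64): √(2.56/102) = 0.158.

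Filling should therefore lie between 0.153 and 0.158, and deletion should lie above both.

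**Simulation.** 4,000 trials of 51 per arm, comparing a linear model on complete cases with a pooled-mean fill plus missing indicator. The values sit slightly above the approximation because the covariate coefficients are estimated too. Power at the planned effect of 0.5 comes from the noncentral t distribution with noncentrality 0.5/SE, two-sided 5%. The degrees of freedom are 88 and 78 for deletion (92 − 4 and 82 − 4) and 97 for filling (102 − 5).

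| Blank on one covariate | SE, deletion | SE, fill | Power, deletion | Power, fill |
|---|---|---|---|---|
| 10% | 0.163 | 0.156 | 86% (0.5/0.163 = 3.07) | 89% (0.5/0.156 = 3.21) |
| 20% | 0.174 | 0.157 | 81% (0.5/0.174 = 2.87) | 88% (0.5/0.157 = 3.18) |

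Deletion raises the SE by about 4% (0.163/0.156 = 1.045) and 11% (0.174/0.157 = 1.108).

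The 20% row need not come from one item. Two covariates, each blank in 10% of pairs independently, would delete 1 − 0.9² = 19%.

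**The case against.** The strongest reply is that nothing is shown to be lost. The article never says that measured pairs are dropped, it gives no missing rate, and its promise to use all available data points the other way. {18a} says that trained data collectors gather the data in a uniform way, so blanks may be rare. Adjustment is conditional, and no covariate beyond age and sex is named; income and education are only examples of what might be used. Even at 20% blanks, power at the planned effect stays above 80% under the assumptions used here. All of this stands, and it limits the point to a conditional loss in secondary use of the data. It does not remove the conflict: where a covariate is blank, the two sentences of {20c} cannot both be followed in that model. Nor can the matter simply be left to an analysis plan, because a plan that filled covariates would contradict the published rule.

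A reader might infer three stronger things that the documents do not support.

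- *That the main comparison loses pairs.* It does not; the tests named in {20a} need no covariate.
- *That a single blank item removes a mother from the knowledge, attitude and practice analysis, or lowers her score.* {18a} says only: "Using a questionnaire with confirmed psychometric properties, the mothers’ nutritional knowledge, attitude, and practice will be assessed". The scoring rule is not shown and may sit with the instrument or the analysis plan. Scoring from answered items could also fit the promise to use all available data.
- *That deletion biases the comparison.* Blanks that arise before randomisation cannot, by themselves, favour an arm, and nothing in the documents shows that mothers with blanks differ from the others. The demonstrable cost is precision.

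**Conclusion.** The point holds in a limited form. The unqualified rule in {20c} would force an adjusted model to omit measured pairs with a blank covariate, against the intention stated in the same section. It touches only adjusted models that include a questionnaire-based characteristic other than age and sex.

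Under the assumed 10–20% blanks and covariate strengths, the cost is 3 to 7 percentage points of two-sided power at the planned effect. With few blanks it would be close to nothing, and with blanks on several covariates it would add up. This is a cheap improvement to a stated rule, not a threat to the trial's main result.

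**What to change.** Limit the no-imputation rule in {20c} to outcomes missing at 3 months, and add one sentence:

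> Missing baseline covariates are filled with the pooled mean plus a missing indicator (continuous) or a *not stated* category (categorical), without regard to arm or outcome, so that every pair with an observed outcome stays in the adjusted model.

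Scoring of the knowledge, attitude and practice questionnaire should follow the instrument's own rule and needs no change here.

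The cost is one changed sentence, one added sentence and a few lines of code. The downside is a few extra model terms, which use up degrees of freedom; the fill column of the table already includes this for one covariate. The change should be made before anyone sees outcome data by arm.

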#### Plans to give access to the full protocol, participant-level data, and statistical code {31c}

The datasets used and/or analyzed during the current study can be made available by the corresponding author upon reasonable request and in agreement with the research collaboration and data transfer guidelines of the Tabriz University of Medical Sciences, as is the full protocol.

### Oversight and monitoring

#### Composition of the coordinating center and trial steering committee {5d}

The principal investigator is the designer of the trial and responsible for conducting the research. The principal investigator and research physicians are responsible for the recruitment, treatment, and follow-up of the participants. The technology development research fellow is responsible for the design and development of the study application. The staff responsible for recruitment activities are responsible for selecting eligible subjects, ensuring that the recruitment process adheres to the defined criteria and protocols. To supervise the entire study process, a steering committee will be set up. Also, the study team will be in continuous communication to monitor the study’s conduct.

#### Composition of the data monitoring committee, its role, and reporting structure {21a}

Since the trial has a short duration and the treatment regimens are associated with known minimal risks, no data monitoring committee will be established.

#### Adverse event reporting and harms {22}

There will be no adverse events or harm in this study due to the nature of the intervention.

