#### Provisions for post-trial care {30}

No specific post-trial care is planned, as the study is a low-risk intervention. At the end of the study, all participants will be offered a report of their children’s nutritional status from the post-assessment, which will determine whether the children need any specific treatment.

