#### Plans to promote participant retention and complete follow-up {18b}

The research team will provide periodic communications with participants via telephone and text message. Also, they will use methods to improve participant retention, such as reminders for using the application and scheduling appointments for post-intervention visit.

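### The harms section states as fact that no adverse events will occur instead of saying how they are collected, and it does not fit the risk statements elsewhere in the protocol

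*Protocol article*

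**What the plan says.** The section Adverse event reporting and harms {22} is one sentence: "There will be no adverse events or harm in this study due to the nature of the intervention". It describes no collection, assessment or reporting of events.

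Two other sections describe the risk differently. Composition of the data monitoring committee {21a} gives as one reason for having no committee that "the treatment regimens are associated with known minimal risks". Provisions for post-trial care {30} says "No specific post-trial care is planned, as the study is a low-risk intervention".

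The children are aged 2 to 6 and enter with "confirmed malnutrition and underweight using growth charts" (Eligibility criteria {10}). That section sets no lower z-score limit, so the severe category defined in Background and rationale {6a} is not excluded.

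Outcomes {12} names "the change in the growth indicators and mothers’ nutritional knowledge, attitude and practice within the groups, and the differences between the groups". The growth z-scores and the mothers' nutritional literacy "will be measured at baseline and after 3-month follow-up visits". No illness, admission or death outcome is listed. Under {30}, "all participants will be offered a report of their children’s nutritional status from the post-assessment". Contact between visits is described only as a means of retention: "The research team will provide periodic communications with participants via telephone and text message" ({18b}).

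**The concern.** An adverse event is any untoward occurrence during follow-up, whether or not the intervention caused it. Arguing from the nature of the intervention addresses causation at most. It says nothing about whether children will fall ill or be admitted in either arm, and a comparison between arms is how a trial separates background illness from an effect.

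A sentence that forecasts no events gives staff no instruction to ask about them. If the plan is followed as written, illness, admission and death have no route into the data. The trial could then support no statement about harms, favourable or unfavourable, in a group of young children chosen because their nutritional state is poor.

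This is more than a detail that a journal article leaves to the full protocol. The article does address the item, and what it states there cannot be known in advance.

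**Working it through.** **1. The statements side by side.**

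| Section | Risk conveyed |
|---|---|
| Adverse event reporting and harms {22} | none, stated as certain |
| Data monitoring committee {21a} | minimal, therefore not zero |
| Post-trial care {30} | low, therefore not zero |

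The first row cannot be held together with the other two if the words are taken at face value.

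**2. Is the forecast plausible?** The sentence rests on no figure, so there is none to reproduce. The number of children comes from Sample size {14}: 102 evaluable, with 14% added for dropout, 102 × 1.14 = 116.28, stated as 116. At 1:1 allocation that is 116 / 2 = 58 per arm. The protocol gives no event rate, so the per-child 3-month rates p below are assumptions. With independent children, the chance of at least one event is 1 − (1 − p)^116:

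- p = 1%: 1 − 0.99^116 = 69%
- p = 2%: 1 − 0.98^116 = 90%
- p = 5%: 1 − 0.95^116 = 99.7%

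Even at the lowest of these rates, an event is more likely than not.

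**3. Could the trial show the certainty it asserts?** Suppose events were fully recorded and none occurred. The one-sided 95% upper limit on the true rate is 1 − 0.05^(1/n):

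- n = 116: 2.5%
- n = 58 (one arm): 5.0%
- n = 51 (completers planned in one arm): 5.7%

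These limits apply to any groups of these sizes. They do not measure the defect. They show only that a claim of no harm lies beyond what this trial could establish even with perfect recording.

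**4. What do the planned data capture?** Growth z-scores at baseline and 3 months are compared between arms with a t-test or Mann–Whitney test (Statistical methods {20a}). That captures average worsening in children who are measured at 3 months. It does not capture:

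- illness, admission or death, which are not listed outcomes in {12};
- how many individual children worsened, which a comparison of group averages does not report;
- children who do not return. The sample size plan allows for 116 − 102 = 14 of them, and 14% of 116 is 16.24, so about 14 to 16. Section {11b} lets the team remove children who do not cooperate or cannot be traced, and {20c} rules out imputation. A child who leaves because of illness would have no 3-month outcome data.

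**The case against.** The strongest reply is that this is an educational app added to usual care, with concomitant care unrestricted ({11d}) and research physicians responsible for treatment and follow-up ({5d}). Nutritional worsening is the harm of most interest, and it is what the trial measures, with blinded outcome assessors ({17a}). The risk wording may be merely loose: {21a} speaks of treatment regimens in the plural and may include usual care, while {22} speaks of the intervention. No planned efficacy estimate depends on the sentence.

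Much of this stands, and it limits the point. A reader might infer any of the following, and the documents do not support them:

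- *That the trial will report a safety result it never measured.* No safety outcome, analysis or conclusion is planned. The problem arises only if a later report cites an absence of harm.
- *That recording is ruled out.* The sentence does not forbid it. Collection is simply not described, and the lack of a route is an inference, though a fair one.
- *That a difference between arms in growth worsening would go unseen.* Average worsening is compared between arms at 3 months. What is missing is the count of children who worsened, and the children who do not return.
- *That the app could delay attendance at a clinic.* Nothing in the document indicates this.

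The loose-wording defence helps with {21a} but less with {30}, which calls the study itself a low-risk intervention. It does not rescue {22}, where events of any cause are said not to occur. Measuring growth does not replace asking about illness, admission and death.

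**Conclusion.** Wrong as written. The harms section asserts an absence of adverse events that cannot be assumed for malnourished, underweight children followed for 3 months. It does not fit the low-risk and minimal-risk statements in {30} and {21a}, and it leaves the trial unable to support any statement about harms.

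The size cannot be given as an event rate, because the document supplies none. Under the assumed 3-month rates of 1% to 5% per child, with independent children, the forecast would prove false with probability 69% to 99.7%. The effect is confined to harms: the efficacy comparison is unaffected. The conclusion rests on the usual definition of an adverse event as an untoward occurrence of any cause, and on the article's own wording of {22}.

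**What to change.** Replace the sentence in {22} with text along these lines: *Risk from the intervention is expected to be minimal. Illness, hospital admission and death since baseline are asked about with the same questions in both arms at the 3-month visit, by the blinded outcome assessors, and by the same telephone call in both arms for those who do not attend. Results are reported by randomised arm.*

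From data already collected, also report by arm the number of children whose weight-for-height or BMI-for-age z-score moved to a worse category of {6a}, naming the index for each count. State the cut-points as −1, −2 and −3, because the bands as printed leave gaps between −1.9 and −2 and between −2.9 and −3. A move from −1.9 to −2.0 would count, so treat this as a descriptive table beside the z-score changes.

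Do not rely on the retention contacts in {18b} for collection. They have no stated schedule and include reminders to use the app, which can apply only to the app arm, and the research team is unblinded ({17a}). Events could then be counted more fully in one arm. Mothers also know their allocation, so reported minor illness will be less robust than admission or death.

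Reconcile {21a}, {22} and {30} so that all three describe the same level of risk.

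The cost is a few questions at an existing visit, a call to non-attenders and one table. Trial status expects completion by July 10, 2023. If follow-up has ended, the report can still tabulate worsening by growth category and should say that other harms were not systematically collected.
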